### Data collection

Assessing how facilitation supports the integration of surgical prophylaxis guidelines is key to measuring our workshop’s impact. To do so, we will track proximal implementation outcomes (acceptability, reach, and reaction) after training, as well as distal outcomes (e.g., order set changes, facilitation techniques) at 6, 12, and 18 months for all hospitals that participate in the training. For a minimum of 20 hospitals participating in NISQIP-P, we will evaluate key outcomes over time using a quasi-experimental time-series design, comparing three years pre- (2022–2024) and post-intervention (2025–2027). This approach balances internal validity with real-world feasibility and allows for detecting meaningful clinical effects.

#### Baseline data

##### Individual participant survey

Upon registration for the facilitation workshop, each participant will be invited to complete a survey that will collect data on their professional roles, experience, affiliation, and formal training in antimicrobial stewardship. Additionally, it will assess their engagement in stewardship decisions, and primary responsibilities related to antimicrobial use.

##### Hospital survey

Each participating hospital will be required to complete a characteristics survey, to be filled out by the ASP team member most familiar with the hospital. This survey will collect data on hospital size (e.g., number of beds, surgical volume) and details about the ASP program, including the strategies implemented, locations of implementation (e.g., intensive care units, emergency department), and evaluation metrics used. Additionally, the survey will gather specific information on ASP efforts to reduce post-operative antibiotic use in various surgical subspecialties.

#### Implementation data

##### Training feedback and evaluation survey

The Kirkpatrick framework will guide our assessment, evaluating training outcomes across four levels: Reaction (participant satisfaction), Learning (knowledge, attitude, and practice change), Behavior (application of learning), and Results (overall impact on performance or outcomes) [27]. Our post-training survey will assess the first two levels: Reaction and Learning. To assess participant satisfaction (Reaction), we will include ten items adapted from a previous assessment of workshop-based practice facilitation resources [16, 28]. To measure knowledge, and practice changes (Learning), participants will respond on a 5-point Likert scale, indicating their level of agreement or disagreement with statements assessing their knowledge, attitudes, and practices, related to facilitation strategies and antibiotic prophylaxis, before and after the workshop (see Supplementary File 1). The survey instrument was developed to align with the facilitation training modules and content (see Table 2). Data will be collected from workshop participants via a survey delivered through REDCap. A retrospective post-test survey will be used to assess both training and implementation outcomes [29, 30]. Participants will complete the survey upon finishing the workshop and will be asked to retrospectively evaluate their knowledge, attitude, and practices before the workshop and how these may have changed as a result of their participation. This approach helps mitigate potential biases in self-reporting that may arise with traditional pre-survey assessments and minimizes the under- or overestimation of initial knowledge [30]. It also simplifies the evaluation process, particularly when collecting pre-survey data is challenging [29].

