### Facilitation workshop

#### Workshop updates and adaptation

In the first six months of the study, we will refine and consolidate our baseline order set and facilitation workshop to enhance scalability and accessibility. Participant feedback from our Operatic 1.0 trial has identified key improvements, including more team-based discussions, additional materials, reduced time commitment, and alignment with the latest evidence on de-implementation, facilitation, and surgical prophylaxis. To improve feasibility and dissemination, we will incorporate continuing medical education (CME) credits through Nationwide Children’s Hospital’s CME department, and offer a self-paced, asynchronous format alongside the live webinar. To address concerns about the workshop’s time demands (previously eight hours over four weeks), we aim to streamline it to three hours delivered in just one session instead of four. We will pre-record didactic content and seek permission to share interactive elements, such as role-playing exercises, ensuring a balance between structured learning and collaboration.

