##### Order sets review

To evaluate Behavior and Results domains of our evaluation model, an assessment will be conducted through 10-min structured interviews approximately 6-, 12-, and 18-months post-workshop training. An interview guide is provided in Supplementary File 2. Based on our experience from our Operatic 1.0 trial, this time interval is sufficient for ASPs to implement order set modifications across different surgical specialties, and participants are generally able to recall the work they have accomplished. The interview will inquire whether an order set modification was made, or a new order set developed (Yes/No, and number). For each impacted order set, we will inquire about the targeted procedure, the previous duration (no post-op antibiotics, 24 h or less, 25–48 h, or 48 h or more), and any changes in duration (eliminated, shortened, or no change). If the post-operative duration has been shortened, we will specify to what extent: no post-op antibiotics, 24 h or less, or 25–48 h. We anticipate some loss to follow-up due to staff turnover. In such cases, we will attempt to identify an alternative respondent, describe the study, and determine whether guideline integration through order set changes has continued.

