##### Knowledge, attitude, and practices change

We hypothesize that participants' knowledge, attitude, and practices regarding the use of facilitation and order set modifications to improve antibiotic prescribing guideline adherence will improve from pre- to post-workshop training. First, to assess the reliability of the scale and subscale scores, we will use Cronbach’s alpha. Descriptive statistics and weighted means will be applied to compare participants’ reactions and learning outcomes pre- and post-workshop using Hedges and Olkin’s method [32]. Paired-sample t-tests will be conducted for each session to evaluate statistically significant differences between (suitably normalized) retrospective pretest and posttest scores.

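### The end-of-workshop survey cannot show that practices improved: in the live format its 'after' practice score can record only intended or perceived practice

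*Protocol article*

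**What the plan says.** Under 'Training feedback and evaluation survey', the protocol article describes a single retrospective post-test form. Participants rate their agreement on a 5-point scale with "statements assessing their knowledge, attitudes, and practices, related to facilitation strategies and antibiotic prophylaxis, before and after the workshop". On timing: "Participants will complete the survey upon finishing the workshop and will be asked to retrospectively evaluate their knowledge, attitude, and practices before the workshop". The same form also asks how these may have changed through taking part.

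That section sets out four levels of evaluation and distinguishes "Learning (knowledge, attitude, and practice change), Behavior (application of learning"). It then limits the form to two of them: "Our post-training survey will assess the first two levels: Reaction and Learning". Behavior and Results are left to the structured interviews under 'Order sets review'.

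Under 'Knowledge, attitude, and practices change', the statistical section states the hypothesis that all three constructs, as they concern facilitation and order set modification "to improve antibiotic prescribing guideline adherence will improve from pre- to post-workshop training". Paired-sample t-tests then compare the retrospective pretest scores with the posttest scores.

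'Workshop updates and adaptation' gives the length. For the earlier eight-hour, four-week workshop, the aim is to "streamline it to three hours delivered in just one session instead of four". A self-paced asynchronous version is offered alongside it.

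**The concern.** A paired test of change needs the second measurement to come after a period in which the change could occur. Knowledge and attitude can shift during a teaching session. Practice, meaning what a steward or surgeon actually does about facilitation and order sets, can shift only once that person is back at work. Here the 'before' rating describes past behaviour, and the 'after' rating is given before any behaviour following a live session exists. Their difference compares something done with something expected.

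What is at stake is the wording of a conclusion. A significant t-test on these scores would, under the stated hypothesis, support a report that practices improved with training. The study's second aim is to find out how the skills and knowledge gained affect guideline adoption, order set change and the use of facilitation techniques. A practice-change result that could not have observed practice would be easy to misread as evidence for that aim.

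**Working it through.** No arithmetic applies: the article gives no sample size, standard deviation, item count or effect size for this test. The check sets its statements on timing side by side.

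1. **When the ratings are taken.** Both the 'before' and the 'after' rating are given at one sitting, as the workshop ends ('Training feedback and evaluation survey').
2. **How far apart the rated states are.** In the live format this is the length of the workshop, planned at about three hours in one session ('Workshop updates and adaptation'). All of that time is training, so clinical work between the two states is nil. For the asynchronous version no elapsed time is given, and a user could work clinically between modules.
3. **What is hypothesised and tested.** Improvement in practices is stated alongside knowledge and attitude, and the paired t-tests use these same scores ('Knowledge, attitude, and practices change').
4. **How long the article allows for change elsewhere.** For the first interview, at about 6 months, 'Order sets review' says "this time interval is sufficient for ASPs to implement order set modifications across different surgical specialties". The primary clinical model places its interruption 12 months after each hospital's first training ('Primary hypothesis'). Neither figure is a minimum time for one person to use a facilitation technique, but both show that effects on practice are expected after the workshop, not within it.
5. **Where the article's own framework puts practice.** The logic model lists knowledge and skills acquisition among the proximal outcomes and places order set adoption and prescribing among the distal ones. The evaluation section, however, puts practice change under Learning while reserving application of learning for Behavior. The proximal hypothesis follows the second classification, not the first.
6. **Whether the stated rationale covers this.** The retrospective form is justified as reducing self-report bias, limiting misjudgement of initial knowledge, and simplifying matters when a pre-survey is hard to collect. All three reasons concern the 'before' rating. None concerns when the 'after' rating is taken.
7. **What is measured later.** Interviews at about 6, 12 and 18 months record, for each affected order set, the previous duration and the change made. 'Data collection' adds facilitation techniques to the outcomes followed at those times. For order sets, then, a recalled comparator exists. For one person's use of facilitation techniques, no baseline is described. The registration survey ("Upon registration for the facilitation workshop, each participant will be invited to complete a survey") covers role, experience, engagement in stewardship decisions and responsibilities, but facilitation techniques are not among its listed contents.

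Steps 1 to 3 establish the point for the live format whatever the item wording: no phrasing lets a form completed at the end of a session observe what happens afterwards.

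**The case against.** The strongest reply is that the protocol already separates learning from behaviour. The form is confined to Reaction and Learning, enacted change is left to the interviews, and nothing says that a Learning score will be reported as Behavior. On this view the matter is one of labels. Much of this stands: the study does have later measures of behaviour. But the hypothesis itself names practices as improving from before to after the workshop and attaches a significance test to them, so the label determines what a positive result will be taken to mean.

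A second reply is that the items are in Supplementary File 1, which is not at hand, and may ask about confidence or perceived ability. That is fair, and it limits what can be said about what the score does measure. It does not turn the score into enacted practice.

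Several stronger readings are tempting, and the document does not support them:

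- A reader might infer that no participant's practice can have changed by the time of the form. Three hours is an aim for the live session, and self-paced users may take longer.
- A reader might infer that the later interviews have no comparator. They ask for each order set's previous duration; the hospital survey collects baseline stewardship efforts by subspecialty; and general linear models of implementation outcomes before and after the workshop are planned as appropriate.
- A reader might infer that a third of the learning effect is unmeasurable. Practices are one of three named constructs, but no item counts or weights are given, so no share follows.
- A reader might conclude that the practice items belong in the registration survey. That would restore the pre-survey design that the authors set aside because of self-report bias. It is a trade-off, not a plain improvement.

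**Conclusion.** The point holds for the practice component of one proximal outcome. In the live format, the paired test cannot show that practices changed, only that participants intend or perceive a change. For asynchronous users the limitation is less strict, to a degree that cannot be judged without elapsed times. The knowledge and attitude components are not affected by this timing problem.

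The conclusion assumes that the live session runs as planned, in one sitting of about three hours, and that the form is completed as it ends. The statement that facilitation techniques lack an individual baseline rests on the article's description of its instruments; the supplementary files could add to it.

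The reach is limited. The primary and secondary clinical endpoints and the power calculation do not use this survey, and the abstract's primary implementation outcome, guideline-congruent order sets, comes from the interviews. The correction is still worth making, because it changes what the study may claim about practice and costs little.

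**What to change.** - In 'Knowledge, attitude, and practices change', limit the hypothesis and the end-of-workshop paired t-tests to knowledge and attitude.
- Report the end-of-workshop practice items descriptively, labelled as intended or perceived practice.
- Base any claim of practice change on the interviews. One way is to ask the same practice items at the existing 6-month interview, in both a before-the-workshop and a current form, and to test that pair. This keeps the retrospective format that the authors prefer and allows time for practice to occur between the two rated states.
- Use only pairs in which the respondent took the workshop. An alternative respondent brought in after staff turnover cannot supply a 'before' rating for someone else.

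The costs are a somewhat longer interview, now planned at 10 minutes; recall of pre-workshop practice over about six months instead of a few hours; and some respondents lost to turnover, which the article already expects. No new contact with participants is needed. If the added items are thought too much, the first two changes alone are enough to prevent the unsupported claim.

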## Statistical analysis plan

### Implementation outcomes

#### Proximal implementation outcomes

##### Facilitation workshop satisfaction and acceptability

Our analysis will address two key questions: (1) participant satisfaction with the mode and delivery of the facilitation workshop and (2) the perceived acceptability of the workshop. To assess these outcomes, we will summarize participant ratings on a five-point Likert scale (1 = strongly disagree, 2 = disagree, 3 = neutral, 4 = agree, 5 = strongly agree) using descriptive statistics (see Supplementary File 1). Open-ended survey responses will be analyzed using a thematic coding approach to identify key qualitative insights [31]. All responses will be systematically reviewed, and themes will be derived inductively by identifying and labeling meaningful units of text relevant to the research objectives.

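### Satisfaction and acceptability are rated only by people who finish the workshop, so the ratings may be overstated, by an amount the plan has no means of showing

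*Protocol article*

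**What the plan says.** Under Training feedback and evaluation survey, the article states: "Our post-training survey will assess the first two levels: Reaction and Learning". It then fixes when that survey is given: "Participants will complete the survey upon finishing the workshop and will be asked to retrospectively evaluate their knowledge, attitude, and practices before the workshop". The Data collection section agrees on timing: "we will track proximal implementation outcomes (acceptability, reach, and reaction) after training".

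The Individual participant survey section describes the only earlier contact with individual participants: "Upon registration for the facilitation workshop, each participant will be invited to complete a survey that will collect data on their professional roles, experience, affiliation". The rest of that section adds stewardship training, involvement in stewardship decisions and responsibilities. No satisfaction or acceptability item is described. The interviews at 6, 12 and 18 months (Order sets review) serve the Behavior and Results levels.

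The first analysis question under Facilitation workshop satisfaction and acceptability is "participant satisfaction with the mode and delivery of the facilitation workshop"; the second is acceptability. Both are answered by descriptive summaries of five-point ratings. On format, Workshop updates and adaptation says the team will "offer a self-paced, asynchronous format alongside the live webinar", and on length, "we aim to streamline it to three hours delivered in just one session instead of four".

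**The concern.** The article's Discussion names wide dissemination of the facilitation strategy as the study's primary goal. Whether people find the training acceptable, and in which mode, is therefore a result that others will read when deciding whether to adopt it. A person who begins and gives up may hold exactly the view that the acceptability question seeks, for example that the training is too long or not useful. Under the stated timing, that view is not collected.

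The matter is more pointed here because time demands were a complaint about the earlier workshop, and the shorter, self-paced option is part of the response. People who had time to finish cannot by themselves show whether that response worked. The self-paced version is also open for continuing access, so someone can leave it part-way without any event that would prompt a survey.

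The article plans for loss elsewhere. It seeks an alternative respondent when an interviewee is lost, names attrition chiefly for the follow-up interviews, and places its missing-data rule under Clinical outcomes. Workshop non-completion is not discussed.

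**Working it through.** **Who supplies a rating.** The instruments side by side:

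| Instrument | When | Satisfaction or acceptability items described? | Reaches people who stop? |
|---|---|---|---|
| Individual participant survey | Registration | No | Yes |
| Training feedback and evaluation survey | On finishing | Yes | No |
| Structured interviews | 6, 12, 18 months | No | Not stated |

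No row both reaches stoppers and asks for these ratings.

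**Inputs from the article.** Planned live places: 4 sessions a year × 2 years × about 20 = about 160. No asynchronous enrolment figure and no completion rate for either format is given. There is therefore no stated figure to reproduce.

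**Formula.** Let *c* be the share of starters who finish, *F* the rating among finishers and *S* the rating stoppers would have given. The value among all starters is *cF* + (1 − *c*)*S*. The report shows *F*, so

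overstatement = *F* − [*cF* + (1 − *c*)*S*] = (1 − *c*)(*F* − *S*).

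**Share finding the workshop acceptable (assumed *F* = 90%).**

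- *S* = 90%, any *c*: overstatement 0.
- *c* = 100%, any *S*: overstatement 0.
- *S* = 50%, *c* = 80%: all starters 0.80 × 0.90 + 0.20 × 0.50 = 0.82, so 90% is reported against 82%, a gap of 8 points.
- *S* = 50%, *c* = 60%: all starters 0.60 × 0.90 + 0.40 × 0.50 = 0.74, so 90% is reported against 74%, a gap of 16 points.
- *S* = 70%, *c* = 90%: 0.10 × 0.20 = 0.02, a gap of 2 points.

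**Mean on the 1 to 5 scale (assumed *F* = 4.3, *S* = 3.3).**

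- *c* = 90%: 0.10 × 1.0 = 0.10.
- *c* = 70%: 0.30 × 1.0 = 0.30.
- *c* = 50%: 0.50 × 1.0 = 0.50.

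The result runs from nothing to a gap large enough to change how the training is described. It depends on *c* and *S*. The registration survey and the listing of reach as an outcome suggest that *c* could be counted. Nothing described in the article would supply *S*.

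**The case against.** The strongest reply is that end-of-training feedback is the ordinary way to measure reaction, and that the bias is supposed rather than shown. The workshop has been cut from eight hours over four weeks to three hours in one session. It carries continuing education credit, and completion opens access to collaborative meetings. Drop-out may therefore be low, and busy clinicians may stop for reasons unrelated to how they rate the training. The ratings are descriptive and do not enter the primary clinical model. The article condenses a fuller protocol, so reminders and reporting denominators may be set out there, and nothing in the article forbids contacting people who stop.

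Most of this stands, and it limits the point to a possibility of unknown size. It does not remove the point, because the article itself fixes the survey at completion and gives no other source for these ratings.

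Three stronger readings are tempting, and the article does not support them:

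- **That the training will look more acceptable than it is, mainly because of the self-paced format.** This needs material non-completion, lower ratings among stoppers and a difference between formats. The article has no data on any of these.
- **That a comparison of live and asynchronous formats could reverse.** This is arithmetically possible, but no such comparison, test or roll-out rule is planned.
- **That the learning result is biased too.** Change in knowledge, attitude and practice is naturally defined among those who took the training. Leaving out stoppers narrows whom the result describes and does not by itself distort it. The retrospective pre-test is also a deliberate choice for which the article gives reasons.

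**Conclusion.** The point holds for satisfaction and acceptability only. As planned, both are measured among finishers, and as statements about everyone who started they may be too high, possibly more in the self-paced format. The size is (1 − completion share) × (finisher minus stopper rating). It is zero at full completion or with equal ratings, and 8 to 16 percentage points at 80% to 60% completion with 90% against 50% acceptable. Those four inputs are assumptions.

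The consequence is modest. It concerns descriptive proximal outcomes and leaves the learning tests, the clinical outcomes and the power calculation untouched. It is an optional improvement, worth making because the present design would not reveal whether the gap is negligible or large.

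**What to change.** **Training feedback and evaluation survey.** Add that the satisfaction and acceptability items, with one item on the reason for stopping, go by REDCap to every participant who started but has not finished by a fixed date.

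**Facilitation workshop satisfaction and acceptability.** Report registered, started and finished counts by format beside the ratings, and label the main ratings as coming from finishers. Describe finishers and stoppers using the registration survey.

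As an optional sensitivity display, add a bound that counts non-responding stoppers as not satisfied. With 90% of finishers satisfied and no stopper replying, the lower bound among all starters would be 0.80 × 0.90 = 72% at 80% completion and 0.60 × 0.90 = 54% at 60% completion. It is informative only when completion is high or stoppers reply, and should be presented as a bound.

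**Cost.** One automatic invitation in a system already in use, and a few lines of text. Response from stoppers is likely to be low, and the acceptability figure may come out less favourable. The form is best set up before sessions begin, since views not collected near the time are hard to recover.
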